### Participant timeline

Figure 1 displays the time schedule of enrolment, interventions, assessments and visits for participating patients.

### Sample size calculation

Since this is a pilot study, a reliable sample size calculation is not feasible. In accordance with recruitment recommendations,^35 36^ a minimum of 15 patients per treatment group will be included. In addition, based on accumulated evidence with 16S rRNA sequencing using MiSeq, Illumina Platform, a sample size of 20 individuals is normally enough to detect relevant differences in the microbiota. Hence, a total sample size of n=30 seems adequate. In order to reduce heterogeneity in faecal transplants, 1 donor will donate faeces to approximately 3 patients, which implicates that 5 donors are needed for 30 patients.

### Statistical analysis

All data will be analysed according to the intention-to-treat principle. Feasibility outcome measures will be presented as proportions at each time point throughout the trial. To assess the efficacy outcomes group differences will be calculated by a mean difference with a 95% CI, using an independent t-test for continuous variables with a parametric distribution or Mann-Whitney U test for continuous variables with a non-parametric distribution. Group differences for categorical variables will be calculated using Fisher’s exact statistics. In addition, data of continues variables will be analysed using mixed models to account for correlations of measurements within the same individual on several time points. Due to the small sample size, baseline values will not be incorporated in these analyses. Significance is set at α=0.05 in all analyses.

Microbiota composition of the faecal samples will be measured by 16S rRNA sequencing and specific genera/species are screened by qPCR. Alfa and beta diversity of faecal samples will be calculated. Cluster analysis and similarity of the microbiota profiles, expressed as Pearson correlation, will be assessed and compared between patients with IBS and healthy donors, between treatment groups and between responders and non-responders. In addition, short-chain fatty acids composition of the faecal samples will be measured.

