A limitation of our study is the small sample size, which allows us to only encounter major effects of the FMT treatment. Furthermore, we decided to include patients with IBS regardless of subtype, leading to a heterogeneous patient population which may affect the efficacy results. Moreover, it is unclear what the effect of bowel lavage is on the efficacy of FMT and on microbiome composition. Studies with and without bowel preparations before FMT demonstrate great efficacy.^38 39^ In addition, it has been shown that bowel preparation can disrupt the colonic ecosystem where the overall microbiome composition recovers to baseline within 14 days after bowel cleansing.^40^ Our efficacy outcome measure is assessed at 12 weeks after the first FMT (and 6 weeks after the second FMT), which minimises the effect that the bowel cleansing can have on the microbiome composition.

In conclusion, the results of this trial will provide preliminary evidence for the use of FMT in adolescents with refractory IBS. The results will inform future larger, double-blind, placebo-controlled trials on the right sample size, on the feasibility of this study design, on efficacy outcome measures and on the potential of the microbiome to be a therapeutic target in IBS.

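### The plan attaches a mean difference with 95% CI to the Mann-Whitney test, which does not estimate one, and names no effect measure or interval beside Fisher's test for the pain responder outcome

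*Protocol article*

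**What the plan says.** All of the analysis wording is in the Statistical analysis section of the protocol article.

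- For continuous measures of efficacy the text reads: "group differences will be calculated by a mean difference with a 95% CI, using an independent t-test for continuous variables with a parametric distribution". The sentence then continues "or Mann-Whitney U test for continuous variables with a non-parametric distribution". The opening commitment to a mean difference and interval thus governs both tests.
- Categorical outcomes have a separate sentence: "Group differences for categorical variables will be calculated using Fisher’s exact statistics". It names no effect measure and no interval.
- A further analysis follows for the continuous outcomes: "data of continues variables will be analysed using mixed models to account for correlations of measurements within the same individual on several time points". The article does not say whether this or the two-sample test leads.
- "Significance is set at α=0.05 in all analyses".

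Under Outcomes, feasibility is primary. The proportion with more than 50% reduction in pain intensity and frequency at 12 weeks is secondary and is listed first among the efficacy outcomes. The Sample size calculation section sets a minimum of 15 patients per group, 30 in total, without a power calculation. The Discussion and conclusion section states the intended use: "The results will inform future larger, double-blind, placebo-controlled trials on the right sample size".

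**The concern.** An estimate and the test reported with it should concern the same quantity. The t-test and the mean difference do. Mann-Whitney and the mean difference do not: the estimate that belongs to Mann-Whitney is the Hodges-Lehmann shift, the median of all pairwise differences between the arms. Read literally, the sentence produces, for a skewed outcome, a t-based interval for the mean beside a rank-based p-value, and one may exclude no effect while the other does not.

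For the binary outcome the gap is of another kind. Fisher's p-value says little about the size of an effect with 15 per arm, and a sample size for the next trial needs an effect with its uncertainty. The article asks for an interval for continuous outcomes but not for the efficacy outcome it lists first.

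**Working it through.** The plan has no power-based figure to reproduce. The only arithmetic in the sample size is 2 x 15 = 30, which agrees. Inputs from the article are 15 per arm and α=0.05, taken here as two-sided. It gives no response rates, so all responder counts and rates below are assumptions.

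**1. Mann-Whitney against the mean difference.** One simulated log-normal data set, 15 v 15 (log-scale SD 1, log-scale shift 0.7), gave:

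| Quantity | Estimate | 95% CI |
|---|---|---|
| Mean difference (t-based) | 20.6 | -0.9 to 42.1 |
| Hodges-Lehmann shift (Mann-Whitney p=0.089) | 13.1 | -1.9 to 27.9 |

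These are different quantities from the same data. The matching interval is easy to obtain. There are 15 x 15 = 225 pairwise differences, and inverting the exact test takes the 65th and 161st of them in order.

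In simulated skewed data at 15 per arm, the t-based result and Mann-Whitney disagreed on significance about 21% of the time. The rate depends on the assumptions. A check with 10,000 log-normal data sets per setting (log-scale SD 1) gave 4%, 13%, 19% and 23% disagreement at log-scale shifts of 0, 0.5, 0.7 and 1.0.

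**2. Fisher's test at 15 per arm.** Summing the probability of every 16 x 16 table with p<0.05, under a common response rate, gives the actual size of the nominal 5% test:

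| Common response rate | Actual size |
|---|---|
| 0.2 | 1.67% |
| 0.3 | 1.70% |
| 0.4 | 1.61% |
| 0.5 | 1.65% |

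The smallest significant splits are 0 v 5, 1 v 7, 2 v 9, 3 v 10 and 4 v 11. With true rates of 20% and 60%, power is about 45%.

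**3. One worked result, 3/15 v 9/15.**

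- Fisher: 12 responders among 30, so C(30,12) = 86,493,225 allocations. The tail with 9 or more in one arm is 2,277,275 + 315,315 + 20,475 + 455 = 2,613,520. The other tail is equal by symmetry. p = 2 x 2,613,520 / 86,493,225 = 0.060.
- Risk difference: 0.600 - 0.200 = 0.400.
- Wilson 95% limits: 0.357 to 0.802 for 9/15, and 0.070 to 0.452 for 3/15.
- Newcombe lower limit: 0.400 - √[(0.600-0.357)² + (0.452-0.200)²] = 0.400 - 0.350 = 0.050.
- Newcombe upper limit: 0.400 + √[(0.802-0.600)² + (0.200-0.070)²] = 0.400 + 0.240 = 0.640.

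The conditional exact odds ratio, which goes with Fisher's test, is 5.6 (95% CI 0.94 to 44.9).

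**4. Other assumed results, 15 per arm.**

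| Responders | Fisher p | Risk difference (Newcombe 95% CI), points |
|---|---|---|
| 6 v 3 | 0.43 | +20 (-12 to +48) |
| 8 v 4 | 0.26 | +27 (-8 to +54) |
| 10 v 4 | 0.066 | +40 (+5 to +64) |
| 10 v 3 | 0.025 | +47 (+11 to +69) |

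In each case the interval tells the planner of the next trial much more than the p-value does.

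**The case against.** The strongest reply is that little is lost. The mixed models cover the continuous variables and return group differences with intervals. A reader might infer that skewed outcomes end with a p-value only; the planned mixed models rule that out. This part of the reply stands.

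Nor is the Fisher sentence a broken promise. The mean difference belongs to the sentence on continuous variables, and the categorical sentence promises nothing of the kind. Fisher's test can be accompanied by an exact odds ratio interval, and the wording does not exclude one. A condensed article may leave the effect measure to the full protocol or analysis plan. All of this stands, and it reduces the second half of the point to an unnamed measure.

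A reader might also infer that the pilot cannot inform a later sample size. That goes too far: the outcome is defined as a proportion, and an interval can be computed from two reported proportions and their denominators.

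The figures need care as well. Fisher's small actual size shows that the test is conservative, not that an interval is missing. The 3 v 9 contrast sets an exact test against an approximate interval, and the matching exact odds ratio interval includes 1, in line with p=0.06. The article does not say how such a result would be described, and its Discussion and conclusion section already concedes that only major effects can be seen.

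Finally, one might charge that the choice between t-test and Mann-Whitney will be driven by the observed data. The article describes no normality check, so that is an inference.

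What the reply does not remove is the pairing of a mean difference with Mann-Whitney. That is stated in the text, not left to another document.

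**Conclusion.** The point holds in a limited form and is modest in size. The article pairs a mean difference and its interval with a test that does not estimate a mean difference. For skewed outcomes the interval and p-value could then disagree: about one time in five in simulation, ranging from 4% to 23% over the shifts tried. These rates rest on assumed log-normal data, since the article gives no distributions.

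Separately, the leading efficacy outcome, which is secondary, is given a test but no effect measure or interval, in a pilot meant to guide a later sample size. With assumed counts of 3/15 v 9/15, p=0.06 would stand beside +40 points (95% CI +5 to +64).

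The documents do not support the stronger readings: that skewed outcomes have no estimate at all, that the Fisher sentence contradicts the mean-difference sentence, or that the trial cannot inform its successor. No figure stated in the article changes.

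**What to change.** Three changes of wording in the Statistical analysis section:

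1. Name the mixed model, with its group difference and 95% CI, as the lead analysis for continuous outcomes.
2. Wherever Mann-Whitney is kept, report the Hodges-Lehmann shift with 95% CI, or a bootstrap CI for the mean difference, in place of a t-based mean difference.
3. For the responder outcome, report the risk difference with a Newcombe or Miettinen-Nurminen 95% CI beside Fisher's p-value.

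If the full protocol or analysis plan already says this, bringing the article's wording into line is enough. The plan's decision to leave out baseline values is a separate matter and is not touched here.

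The cost is analysis wording only: standard software, no new data and no change to sample size or conduct. The small downside is that an approximate interval may occasionally disagree with Fisher's p-value, as in the 3 v 9 and 10 v 4 examples. One sentence stating that the interval is the main result and the p-value supportive would deal with that.

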**Methods and analysis:**

This randomised, placebo-controlled single-centre pilot study will assess feasibility and efficacy of FMT in 30 adolescents (16–21 years) with refractory IBS. Patients will be randomly allocated (1:1) to receive two allogeneic (healthy donor) or two autologous (own) faecal infusions at baseline and after 6 weeks. Primary outcomes will assess feasibility, including patient and donor recruitment, adherence and incidence rates of adverse events. To evaluate clinical efficacy, secondary outcomes will include the proportion of patients with at least >50% reduction of their abdominal pain intensity and frequency 12 weeks after the first FMT, and after 6-month and 12-month follow-up. Other outcomes comprise changes in faecal gut microbiota composition, quality of life, depression and anxiety, school or work absenteeism and adequate relief, measured directly after FMTs and after 6 and 12 months of follow-up.

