**Figure 1 F1:**
[figure not shown]
Trial design. After adolescents sign the informed consent form (T-2), patients complete the baseline pain diary, the Irritable Bowel Syndrome Severity Scoring System (IBS-SSS) and deliver stool samples and blood samples for eligibility screening. At T0, adolescents are randomised in the allogeneic or autologous faecal microbiota transplantation (FMT) group.

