### Randomisation, blinding and treatment allocation

Randomisation will be done by a computerised random-number generator in the Electronic Data Capture system Castor EDC in a 1:1 ratio to one of the following two treatment arms:

Allogeneic faecal infusions at t=0 weeks and t=6 weeks.Autologous faecal infusions at t=0 weeks and t=6 weeks.

Randomly permuted blocks of size 2 and 4 will be used with no stratification. On the day of faecal transplantation, both patient and donors will deliver faeces produced that morning. Randomisation will be performed by one of the ‘randomisation assistants’, who is designated to this task. To guarantee blinding, the randomisation assistant will make sure the randomised treatment is not traceable to the donor or the patient. The blinded faeces will be brought to the laboratory, where the preparation of the faeces will be done by one of the investigators. Detailed information about the preparation process is outlined under ‘FMT procedure’. During the second FMT at 6 weeks, faeces will be processed according to the randomisation performed on the first transplantation day. The randomisation assistant is the only person who will know which treatment the patient will be given and will have no role in further parts of the study. The randomisation list will be kept under secured access by Castor EDC. In case of an emergency, the study treatment can be unblinded after consultation of the principal investigator.

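### The small sample is not a valid reason to leave baseline values out of the continuous efficacy analyses; adjusting for a collected baseline costs at most about 4% in variance and may save far more

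*Protocol article*

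**What the plan says.** For continuous efficacy outcomes, the Statistical analysis section plans group comparisons "using an independent t-test for continuous variables with a parametric distribution or Mann-Whitney U test for continuous variables with a non-parametric distribution". It adds that "data of continues variables will be analysed using mixed models to account for correlations of measurements within the same individual on several time points". The next sentence reads: "Due to the small sample size, baseline values will not be incorporated in these analyses". No other reason is given. The section closes with "Significance is set at α=0.05 in all analyses".

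Three other places bear on this:

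- Sample size calculation: "a minimum of 15 patients per treatment group will be included", for a total of 30.
- Randomisation, blinding and treatment allocation: "Randomly permuted blocks of size 2 and 4 will be used with no stratification". The design therefore does nothing to balance baseline severity between the arms.
- Figure 1 legend: after consent and before randomisation, "patients complete the baseline pain diary, the Irritable Bowel Syndrome Severity Scoring System (IBS-SSS"), and they also deliver stool and blood samples. A baseline therefore exists for at least the pain and IBS-SSS scores.

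The leading efficacy outcome is binary: a reduction of more than 50% in pain intensity and frequency relative to baseline. Categorical outcomes are compared by Fisher's exact methods. The primary objective is feasibility.

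**The concern.** The article makes a fixed choice and gives one reason for it, so this is not a detail left to a fuller plan. The reason implies that 30 patients are too few to afford a baseline covariate. One covariate costs one degree of freedom. What it returns depends on how strongly the baseline value predicts follow-up, and repeated scores on the same symptom scale in the same patient are usually correlated to some degree.

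Two things are at stake. The first is precision: the Discussion says the results should inform the sample size and efficacy measures of larger trials, and it concedes that only major effects can be seen with this sample. The second is chance imbalance: with 15 per arm and no stratification, the arms can start at visibly different severity, and a comparison of raw follow-up values attributes part of that difference to treatment.

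**Working it through.** **Inputs from the article.** 15 per arm, 1:1 allocation, no stratification, α = 0.05 (taken as two-sided, since 95% confidence intervals are planned). The stated total reproduces: 2 × 15 = 30. No effect size, SD or power is given, so effects are in SD units of the outcome.

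**Assumption.** The baseline-to-follow-up correlation ρ is not given, so a range is shown. The calculation is for one follow-up visit with complete, normally distributed data.

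**Step 1: cost and gain of one covariate.** The unadjusted t-test has 28 degrees of freedom and analysis of covariance (ANCOVA) has 27. The ratio of the variance of the adjusted to the unadjusted effect estimate is

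(1 − ρ²) × (N − 3)/(N − 4) = (1 − ρ²) × 27/26.

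- ρ = 0: 1 × 1.038 = 1.04
- ρ = 0.3: 0.91 × 1.038 = 0.945
- ρ = 0.5: 0.75 × 1.038 = 0.779
- ρ = 0.7: 0.51 × 1.038 = 0.530

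Break-even on variance is at ρ = √(1 − 26/27) = 0.19. On confidence interval width, allowing for the lost degree of freedom, it is 0.20.

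**Step 2: what this means for the trial.** Noncentral t, two-sided 0.05:

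| ρ (assumed) | Variance ratio | CI width ratio | Difference detectable at 80% power | Power at 0.8 SD | Equivalent unadjusted N |
|---|---|---|---|---|---|
| unadjusted | 1 | 1 | 1.06 SD | 56% | 30 |
| 0 | 1.04 | 1.02 | 1.08 SD | 55% | 29 |
| 0.2 | 1.00 | 1.00 | 1.06 SD | 56% | 30 |
| 0.3 | 0.95 | 0.97 | 1.03 SD | 58% | 32 |
| 0.5 | 0.78 | 0.88 | 0.94 SD | 67% | 39 |
| 0.7 | 0.53 | 0.73 | 0.77 SD | 83% | 57 |

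A simulation with 40,000 trials per setting, run at ρ = 0, 0.3, 0.5 and 0.7, agrees: power at 0.8 SD was about 56% unadjusted and 55%, 58%, 67% and 83% adjusted.

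**Step 3: chance imbalance.** The SD of the baseline mean difference is √(2/15) = 0.365 SD. The probability that it exceeds 0.5 SD in either direction is 2 × [1 − Φ(0.5/0.365)] = 0.17. Given an imbalance of 0.5 SD, the unadjusted follow-up difference shifts by ρ × 0.5 SD, which is 0.25 SD at ρ = 0.5.

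Among simulated null trials with an imbalance above 0.5 SD, the unadjusted test rejected in 7%, 11% and 19% of trials at ρ = 0.3, 0.5 and 0.7. ANCOVA rejected in about 5% each time. Over all simulated null trials, both tests rejected in about 5%.

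**Step 4: if the t-tests are run on change scores.** The variance ratio against follow-up values alone is then 2(1 − ρ): 1.4 at ρ = 0.3, 1.0 at 0.5 and 0.6 at 0.7. ANCOVA has 0.95, 0.78 and 0.53, so it is more precise at each of these values.

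**The case against.** The best defence is that the unadjusted analysis is valid: it is unbiased over randomisation and holds its type I error at 5%. Efficacy is secondary, and the article discloses the limits of its sample. All of that stands, and it limits the severity. It does not rescue the stated reason.

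A reader might infer more than the article supports:

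- **That every continuous comparison loses precision.** Below a correlation of about 0.2, adjustment costs a little. Follow-up runs to 48 weeks, and the entry threshold of 30 mm on the pain scale restricts the baseline range, which may lower the correlation for pain.
- **That small trials gain most from adjustment.** At ρ = 0.5 the variance ratio is 0.78 at N = 30 and 0.75 at N = 400, so the proportional gain is slightly smaller here. What is larger at N = 30 is the absolute variance saved (0.029 against 0.0025 SD²) and the typical imbalance (0.37 against 0.10 SD).
- **That all efficacy analyses ignore baseline.** The responder outcome uses it by definition. The sentence follows directly on the mixed models and may refer only to them, so raw follow-up values in the t-tests are not certain.
- **That effects on change cannot be estimated.** The abstract says "Other outcomes comprise changes in faecal gut microbiota composition, quality of life, depression and anxiety". Under randomisation, however, the difference between arms in follow-up means has the same expectation as the difference in mean change. The article should still say how change outcomes are analysed.
- **That every baseline is at hand.** The legend confirms pain, IBS-SSS, stool and blood. Baseline quality of life and depression or anxiety scores are not confirmed in the visible text, and the figure itself is not shown.

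**Conclusion.** The concern holds in a limited form. The article excludes baseline values from the continuous efficacy analyses, at least from the mixed models, for a reason that is statistically wrong. At 15 per arm the worst-case price of adjustment is about 4% in variance and 2% in interval width. The gain is about 5%, 22% or 47% in variance at correlations of 0.3, 0.5 or 0.7. The size of the gain rests entirely on these assumed correlations; the conclusion that the small sample is no obstacle does not.

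The exposure to chance imbalance is conditional. It matters for the one allocation that occurs, with a 17% chance per outcome of a difference above 0.5 SD, and it does not make the planned tests invalid. No feasibility conclusion depends on it. Severity is moderate.

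**What to change.** Delete the sentence. For each continuous outcome with a baseline measurement, such as total IBS-SSS and the pain scores, include the patient's own baseline value as a covariate. This can be done by ANCOVA, in the mixed model already planned, or in a constrained longitudinal model with baseline as the first visit. Report the 12-week contrast from that model. The t-test and Mann-Whitney test can remain as supporting analyses. State how outcomes described as changes are analysed. The responder analysis needs no change on this account.

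The cost is wording and one degree of freedom per model, with a slight loss of precision for any outcome whose correlation is below about 0.2. With baseline as a covariate, a patient lacking that value could drop out of the model, so the handling of a missing baseline should be settled in advance; the constrained longitudinal model avoids that loss. Patients with partial follow-up are already kept by the planned mixed model, so that is not a gain of this change.
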